#### Placebo memantine

Placebo will be dosed according to the same schedule as memantine, including titration and taper periods, and dose individualisation. Placebo memantine tablets will differ from active memantine tablets only in the absence of the active ingredient and will be indistinguishable by sight, touch, or taste. The matched placebo is PROSOLV EASYtab SP (JRS Pharma, Weissenborn, Germany). It consists of 95–98% microcrystalline cellulose, 1.5–2.5% colloidal silicon dioxide, 0.5–2% sodium starch glycolate, and 0.3–1.0% sodium stearyl fumarate.

Trial medicines will be manufactured, packaged, and labelled to comply with Good Manufacturing Practice. The trial medicine will be dispensed by an independent trial pharmacist direct to participants’ homes. Each trial medicine kit will include a pill cutter to halve tablets during titration and taper periods, a medication schedule, and medication instructions.

#### Graded motor imagery

Graded motor imagery is a progressive rehabilitation program thought to sequentially activate brain regions associated with motor planning and execution. The components of the graded motor imagery program include (i) left/right limb judgments (implicit motor imagery), (ii) imagined limb movements (explicit motor imagery), (iii) mirror therapy, and (iv) functional re-engagement and loading of the limb. See [22] for additional detail. The intervention is supported by education about CRPS and patient-led goal-setting.

Participants will individually receive 7, 1-h sessions over 16 weeks delivered by physiotherapists via telehealth (Zoom, USA). The first 4 sessions will be scheduled at approximately 2-week intervals, and the final 3 sessions will be scheduled at approximately 3-week intervals. Participants may be prescribed up to 1 h of home activities daily. The intervention progression follows a standard progression protocol, with mandatory advancement at each treatment session. Eligible graded motor imagery providers will be registered physiotherapists with experience treating CRPS who have completed a 2-day training course on graded motor imagery (delivered by training provider Noigroup, Australia). The study team will provide trial clinicians with 20 h of training on the graded motor imagery treatment protocol. Clinicians will be provided with a clinician manual and have access to clinical supervision during the trial.

Participants will receive resources that complement the delivery of the graded motor imagery intervention, including a CRPS pain education book (Complex Regional Pain Syndrome, an Explain Pain Handbook: Protectometer, Noigroup, Australia [developed for this trial, not currently for sale and attracts no royalties]), and access to an e-learning platform (Pathwright, USA), which is used to guide the home activities and direct the weekly intervention schedule. For the implicit motor imagery and mirror therapy activities, participants will receive the commercially available Recognise App, Recognise Flashcards, and a Mirror Box (Noigroup, Australia). The graded motor imagery intervention session schedule is provided in Supplementary Fig. 1. A detailed intervention description will be provided in a separate publication of the intervention program theory.

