## Interventions

### Explanation for the choice of comparators {6b}

An inert placebo will be used as a comparator for memantine to separate the effect of this medicine from non-specific effects of being allocated and taking an oral medicine. Graded motor imagery will be evaluated against no graded motor imagery, as it was not considered possible to implement a sham that is both convincing and inert.

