#### Graded motor imagery

The trial clinicians will individually tailor the graded motor imagery intervention for the study participants based on their symptoms, conceptual understanding of educational content, time, and preferences. Clinicians will determine the dose of each intervention component at each session. The graded motor imagery therapy may be discontinued at the participants’ discretion.

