### Sample size {14}

The sample size calculation was based on a factorial analysis, where interventions are assumed to have independent effects. For the primary outcome of pain intensity at 16 weeks, we will be guided by a between-group difference of 1 point on an 11-point NRS to justify implementation of the interventions as suggested for chronic pain RCTs [55]. For the primary outcome of pain interference at 16 weeks, we will be guided by a between-group difference *T*-score metric of 5 to justify implementation of the interventions.

Using a repeated measures model with outcomes measured at baseline and follow-up timepoints, and with a correlation between adjacent time points of 0.7 [56], 182 participants are required to provide 90% power with a two-sided 2.5% significance level to detect an effect (of memantine compared to placebo, or graded motor imagery compared to no graded motor imagery) of either 1 point on an 11-point NRS for pain intensity, assuming a standard deviation of 2, or 5 *T*-metric points on the PROMIS Pain Interference scale, assuming a standard deviation of 10. Allowing for 10% dropout, we will aim to recruit a total of 204 participants (rounded up from 200.2).

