### Statistical methods for primary and secondary outcomes {20a}

#### Main analysis

All outcomes will be analysed according to the intention to treat principle. The analysis will involve estimation of the marginal mean effect of memantine compared to placebo and the marginal mean effect of graded motor imagery compared to no graded motor imagery on pain intensity and pain interference at 16 weeks. Additional information on the estimands of interest, including handling of intercurrent events, is provided in Table 2. As the trial has dual primary outcomes, interval estimates will be 97.5% confidence intervals. There will be no multiplicity adjustment for the two interventions as the factorial design answers two distinct questions.

**Table 2 Tab2:** Trial estimands

Estimand component	Definition
Interventions to be compared	To estimate the average causal effect of memantine, we will compare the mean outcome of trial participants allocated to receive memantine and graded motor imagery or memantine only with the mean outcome of trial participants allocated to receive placebo and graded motor imagery or placebo only To estimate the average causal effect of graded motor imagery, we will compare the mean outcome of trial participants allocated to receive memantine and graded motor imagery or placebo and graded motor imagery with the mean outcome of participants allocated to receive memantine only or placebo only
Population of interest	Adults with CRPS as defined by the trial eligibility criteria
Outcome of interest	Pain intensity, measured on a 11-point NRS; pain interference, measured with PROMIS pain interference v1.1
Summary measure (population-level)	Mean difference
Intercurrent events	All intercurrent events relating to memantine and graded motor imagery (e.g. intervention discontinuation, use of non-trial treatments) will be handled using a treatment policy strategy

For each of the dual primary outcomes, we will fit a longitudinal mixed-effects model that includes terms for the fixed effects of each intervention, the three follow-up timepoints, the intervention by time interactions, the two-way interaction between the interventions, and the baseline values of the outcome variables. In addition, the models will include terms for the fixed effects of the duration of CRPS (modelled as linear or linear with log transformation) and workplace compensation status, as well as random intercepts for trial participants.

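### If physiotherapists differ in their results, the 97.5% intervals for the graded motor imagery effect will be too narrow, because the stated model has no therapist term

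*Protocol article*

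**What the plan says.** - **Delivery.** Under Intervention description {11a}, Graded motor imagery: "Participants will individually receive 7, 1-h sessions over 16 weeks delivered by physiotherapists via telehealth (Zoom, USA". The same section standardises delivery: "The intervention progression follows a standard progression protocol, with mandatory advancement at each treatment session". It adds a 2-day course, 20 h of trial-specific training, a clinician manual and access to supervision.
- **Discretion.** Under the discontinuation and modification criteria {11b}: "Clinicians will determine the dose of each intervention component at each session".
- **Comparator.** Under choice of comparators {6b}: "Graded motor imagery will be evaluated against no graded motor imagery". There is no sham, so half of the participants have no trial physiotherapist.
- **Model.** Under Main analysis {20a}: "we will fit a longitudinal mixed-effects model that includes terms for the fixed effects of each intervention, the three follow-up timepoints". The list goes on to the interaction terms, baseline, CRPS duration and compensation status, and ends "as well as random intercepts for trial participants". Secondary and safety outcomes follow the same approach.
- **Sample size {14}.** "182 participants are required to provide 90% power with a two-sided 2.5% significance level to detect an effect". No ICC, number of therapists or design effect appears among the inputs.
- **Sensitivity analyses {20b}.** These address the no-interaction assumption and the multi-arm comparisons. Multiple imputation is added under {20c} if enough data are missing. None concerns therapists.

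The Trial status section says that the article includes the statistical analysis plan, so the listed terms are the planned model.

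**The concern.** People treated by the same physiotherapist may have correlated outcomes, through the clinician's skill, emphasis and choice of dose. The participant intercept handles repeated measurements within one person. It does nothing for correlation between people who share a clinician.

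The correlation arises on one side of the imagery comparison only. If it is present, the variance of the imagery-group mean is larger than the model assumes, and the interval falls short of its stated coverage.

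This matters here because General analysis principles rests interpretation on point estimates and the precision shown by confidence intervals, not on significance claims. The abstract also presents imagery as scalable, which looks beyond the clinicians used in the trial.

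The planned blinded preliminary analyses would not bring the problem to light. Randomly permuted dummy allocations break the link between therapist and imagery group.

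**Working it through.** **1. The plan's own figure.** Inputs from Sample size {14}: difference 1, SD 2 (for pain interference 5 and 10, the same standardised effect of 0.5), two-sided 2.5%, power 90%, correlation 0.7 between adjacent time points.

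- Critical values are 2.2414 and 1.2816, and (2.2414 + 1.2816)² = 12.41.
- Total N without correlation = 4 × 12.41 × 2² / 1² = 198.6.
- Multiplying by (1 − r²) for baseline adjustment:

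| Baseline-to-endpoint correlation | Reading | Total N |
|---|---|---|
| 0.7 | 16 weeks is adjacent to baseline | 101.3 |
| 0.7² = 0.49 | the 12-week measure lies between | 150.9 |
| 0.7³ = 0.343 | three steps from baseline | 175.2 (178 with the t distribution) |

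The stated 182 is not reproduced for the 16-week contrast. The nearest variant corresponds to the distance from baseline to 52 weeks, which the article does not say was used. None of these variants contains a therapist design effect.

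**2. Effect of clustering in one arm.** There are 182 / 2 = 91 evaluable participants on each side of the imagery comparison. The number of therapists and the ICC are **assumptions**. So are equal caseloads (91 divided by the number of therapists, rounded to m) and one therapist per participant.

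- Design effect in the imagery groups: D = 1 + (m − 1) × ICC
- Ratio of true to reported standard error: R = √((1 + D) / 2)
- Actual false-positive rate: 2 × (1 − Φ(2.2414 / R)); coverage is one minus this

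| Therapists | m | ICC | D | R | Error (nominal 2.5%) | Coverage (nominal 97.5%) |
|---|---|---|---|---|---|---|
| 8 | 11 | 0.01 | 1.10 | 1.02 | 2.9% | 97.1% |
| 6 | 15 | 0.05 | 1.70 | 1.16 | 5.4% | 94.6% |
| 4 | 23 | 0.05 | 2.10 | 1.25 | 7.2% | 92.8% |

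**3. Check by simulation.** A two-group comparison of means was simulated with 92 per side, SD 2 and 20,000 trials per setting. It is a simplification of the full longitudinal model.

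- At ICC 0.05 the reported standard error stays near 0.29. The true one is 0.32, 0.33, 0.36 and 0.39 with 12, 8, 5 and 3 therapists, and the error rates are 4.1%, 4.8%, 6.7% and 9.5%.
- At ICC 0.01 the error is 2.8% to 3.8%.
- At ICC 0 it is 2.3% to 2.8%, in line with the nominal level.

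**4. Power.** With 91 per side, the unclustered standard error is 2 × √(2/91) × √(1 − r²). Power is Φ(1 / (SE × R) − 2.2414).

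| r | Unclustered SE | Power, R = 1 | Power, R = 1.16 | Power, R = 1.25 |
|---|---|---|---|---|
| 0.7 | 0.212 | 99% | 97% | 94% |
| 0.49 | 0.258 | 95% | 86% | 81% |

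If 182 is instead taken to give exactly 90% without clustering, power is Φ(3.523 / R − 2.2414), which is 79% at R = 1.16 and 72% at R = 1.25. The answer turns on a correlation that the article leaves open.

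**The case against.** The strongest reply is that nothing in the article shows a positive therapist ICC. Delivery is standardised by a fixed progression with compulsory advancement, training, a manual, supervision and an e-learning platform for home activities. Tailoring follows the participant's symptoms, understanding, time and preferences, which is variation between participants and need not create variation between therapists. With many therapists and an ICC near 0.01 the distortion is trivial. This stands as a limit on size. It does not make the ICC zero, since clinicians still choose the dose of each component.

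Second, omitting the term is defensible if inference is confined to these particular therapists. The estimand table neither defines nor excludes a wider population of therapists, but the article nowhere states such a restriction, and its stated aim of guiding international management points the other way.

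Third, with few therapists the variance component is poorly estimated and degrees of freedom are scarce. This also stands, and is why replacing the primary model is not insisted on.

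Two stronger readings are tempting:

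- A reader might infer that the imagery intervals are certainly too narrow for every outcome at every visit. That would need a therapist effect on each outcome out to 52 weeks, and the article shows none.
- A reader might infer that imagery power falls to 79% or 72%. Those figures require 182 to give exactly 90% without clustering. With a baseline-to-16-week correlation of 0.7, power stays above 90% in all three scenarios of step 2.

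**Conclusion.** The concern holds in conditional form. The structure is documented: several physiotherapists, dose set by the clinician, an untreated comparator, a participant intercept as the only random effect, and no allowance for therapist in the sample size or sensitivity analyses. Any positive therapist ICC makes the imagery intervals too narrow.

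The amount cannot be fixed from the article. Over the assumed scenarios of 8 therapists with ICC 0.01 to 4 with ICC 0.05, it runs from negligible (1.02) to material (1.25). Fewer therapists or a higher ICC would make it larger. The memantine main effect is largely unaffected, because memantine is randomised independently of therapist. Loss of power below 90% is not established.

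**What to change.** - Record the treating physiotherapist for each imagery participant. The article mentions session attendance and diaries, but does not say that therapist identity is captured, so this should be confirmed now.
- Before unblinding, pre-specify a partially nested analysis of the imagery contrasts for both primary outcomes: a therapist-level random coefficient on the imagery indicator, above the participant level, with small-sample degrees of freedom (Satterthwaite or Kenward–Roger). At minimum, report it as a sensitivity analysis beside the main model.
- Report the number of therapists and the estimated ICC.
- State in Sample size {14} that the power for imagery assumes no therapist clustering.

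The term should be written down in advance because therapist identity exists only in the imagery groups. Exploring it during the blinded preliminary work would reveal imagery allocation to the statistician. The final assessment is expected in Q2 2027, so there is time.

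The cost is some plan wording, one data field if it is not already held, and one further model. The imagery interval will be somewhat wider, and the therapist variance will be poorly estimated if therapists are few. No extra participants and no change to treatment are needed.

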### Criteria for discontinuing or modifying allocated interventions {11b}

#### Memantine/placebo

The maximum tolerated dose (up to 40 mg/day) will be determined by the participant in consultation with the blinded trial physician and considers the participant’s willingness to continue the drug therapy despite adverse effects. Should participants need to temporarily suspend treatment due to intolerable adverse effects, they will be instructed to cease the medication for 48 h, at which point they will be reviewed by the trial physician. If the intolerable adverse effects have resolved, the participant will be instructed to resume the study medication at the highest tolerated dose before the onset of intolerable adverse effects. If the intolerable adverse effects have not resolved, the participant will be instructed to continue witholding the medication, with review by the trial physician every 48 h. The memantine/placebo therapy may be discontinued at the participant’s or physician’s discretion.

#### Graded motor imagery

The trial clinicians will individually tailor the graded motor imagery intervention for the study participants based on their symptoms, conceptual understanding of educational content, time, and preferences. Clinicians will determine the dose of each intervention component at each session. The graded motor imagery therapy may be discontinued at the participants’ discretion.

### Strategies to improve adherence to interventions {11c}

Adherence to memantine/placebo intervention will be measured via daily self-report medication diaries and pill counting in returned medication kits. Research staff will monitor medication diaries and contact participants who are not taking the study medicines as required to encourage adherence. Adherence to the graded motor imagery intervention will be measured by session attendance and daily self-report therapy diaries. Research staff and trial clinicians will monitor the number of completed graded motor imagery sessions and encourage attendance for participants who miss sessions. Trial clinicians will monitor the amount of home activities done through the e-learning portal and use communication skills to improve adherence when needed.

### Relevant concomitant care permitted or prohibited during the trial {11d}

Participants will be able to continue their usual treatment for CRPS which may include, but is not limited to, pharmacological, psychological, and rehabilitative treatments, excluding those listed in the exclusion criteria. We expect the concomitant use of therapies to be similar across all groups at baseline due to the randomised design of this study. Participants will record all concomitant therapies (and their dose) in healthcare use forms. Participants will be asked not to initiate new treatments during the trial therapy period, but should they do so, they will be asked to inform the study team and record these in the healthcare use forms. Participants will be asked not to access memantine or graded motor imagery outside of the trial.

### Provisions for post-trial care {30}

There will be no provisions for ancillary and post-trial care. Participants wishing to continue or recommence the trial therapies will need to consult their usual treating clinicians. The sponsor, Neuroscience Research Australia, adheres to the principles outlined in the Medicines Australia Guidelines for Compensation for Injury Resulting from Participation in a Company-Sponsored Clinical Trial. Neuroscience Research Australia has a ‘no fault’ compensation policy from UniMutual Clinical trials Protection insurance to the value of AUD$30M. The policy covers bodily injury to any research subject in a clinical trial.

### Outcomes {12}

The study outcome domains comprise those included in the core outcome measurement set for CRPS clinical studies [37]. The outcome measures were selected through consultation with the study’s consumer panel of people with lived experience of CRPS.

#### Primary outcomes

The dual primary outcomes are pain intensity and pain interference. These outcomes were selected by the study consumer panel as they were determined to represent the most important aspects of improvement for CRPS. Pain intensity is the average pain intensity of the affected limb over the previous 7 days assessed using the 11-point numeric rating scale (NRS) [38], with scores of 0 indicating ‘no pain’ and scores of 10 indicating ‘worst imaginable pain’. This scale has demonstrated validity and reliability for use in chronic pain research [39]. Pain interference is assessed using the Patient-Reported Outcomes Measurement Information System (PROMIS) Pain Interference v1.1 [40], measured over the previous 7 days, with higher scores indicating greater pain interference. This measure has demonstrated reliability and validity across different pain populations [40, 41]. Both dual primary outcomes will be assessed as differences in mean final values at 16 weeks post-randomisation.

#### Secondary outcomes

Pain intensity, assessed over the previous 7 days using the 11-point NRS. Collected at 26 and 52 weeks post-randomisation.Pain interference, assessed over the previous 7 days using PROMIS Pain Interference v1.1. Collected at 26 and 52 weeks post-randomisation.Physical function, assessed at present using PROMIS Physical Function v2.0 [42], with higher scores indicating greater physical function. Collected at 16, 26, and 52 weeks post-randomisation.Fatigue, assessed over the previous 7 days using PROMIS Fatigue v1.0 [43], with higher scores indicating greater fatigue. Collected at 16, 26, and 52 weeks post-randomisation.Self-efficacy to manage symptoms, assessed at present using PROMIS Self-Efficacy Manage Symptoms v1.0 [44], with higher scores indicating greater self-efficacy to manage symptoms. Collected at 16, 26, and 52 weeks post-randomisation.Cognitive function, assessed over the previous 7 days using PROMIS Cognitive Function Abilities Subset v2.0 [45], with higher scores indicating greater cognitive function. Collected at 16, 26, and 52 weeks post-randomisation.Depressive symptoms, assessed over the previous 7 days using PROMIS Depression v1.0 [46], with higher scores indicating greater depressive symptoms. Collected at 16, 26, and 52 weeks post-randomisation.Health-related quality of life, assessed over the previous 7 days and ‘generally’ using PROMIS Global Health short form v1.1 [47], with higher scores indicating better health-related quality of life. Collected at 16 and 52 weeks post-randomisation.Pain self-efficacy, assessed at present using Pain Self-Efficacy Questionnaire (two-item short form) (PSEQ-2) [48]. The PSEQ-2 comprises two 7-point Likert scales (total score = 14), with higher scores indicating higher pain self-efficacy. Collected at 16, 26, and 52 weeks post-randomisation.Patient Global Impression of Change [37], assessed at present using a 7-point scale, with higher scores indicating greater improvements. Collected at 16 weeks post-randomisation.CRPS severity, assessed at present using the CRPS Severity Score [49, 50]. The CRPS Severity Score assesses 8 self-report symptoms and 8 clinician-assessed signs (total score = 16), with higher scores indicating greater CRPS severity. Collected at 16 weeks post-randomisation.Cost effectiveness, assessed as prescription and over-the-counter medicines use and visits (yes/no) to a healthcare provider for CRPS. Collected via self-report questionnaires and MBS and PBS data at 16, 26, and 52 weeks post-randomisation.Adverse events, assessed as the number of participants with at least one adverse event, serious adverse event, or specific adverse event (yes/no). Collected during treatment and during follow-up.

Continuous outcomes will be assessed as differences in mean final values at each timepoint; binary outcomes will be assessed as ratios of proportions.

PROMIS instruments use a *T*-score metric, in which 50 is the mean of the reference population and 10 is the standard deviation of that population [51]. All PROMIS scales, except for Global Health short form v1.1, will be measured using computer adaptive tests. Computer adaptive tests use item response theory to provide precise measurement using few items, and allow for scores that are directly comparable across different selections of items [52].

Pain intensity, pain interference, physical function, self-efficacy, and cognitive function will also be measured at 12 weeks to explore the mechanisms by which the graded motor imagery intervention exerts its effects. To evaluate the effect of adhering to the interventions, the following outcomes will also be measured: weekly measures of pain intensity, item 4 of the Credibility/Expectancy Questionnaire [53], Medical Form Confidence (weekly); International Physical Activity Questionnaire Short Form [54] (end of treatment only). See Methods for additional analyses (e.g. subgroup analyses) {20b} for further information.

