The coefficients in the model are conditional on the other factors in the model. However, our primary interest is in the estimation of the marginal effects of the interventions. Point and interval estimates of the marginal effect of each intervention at 16 weeks will be obtained by appropriately weighting the sum of the relevant model coefficients and the elements of the variance-covariance matrix using the -margins- command in Stata. Secondary outcomes and safety outcomes (the number of participants experiencing at least one adverse event, specific adverse events, serious adverse events) will be analysed in the same way except that log binary models will be used for binary outcomes. For each comparison, mean differences or risk ratios, each with 97.5% confidence intervals, will be presented in tables (see Supplementary Tables 2, 3, 4, and 5).

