### Adverse event reporting and harms {22}

Safety monitoring and reporting will be conducted in accordance with the NHMRC guidance on Safety Monitoring and Reporting in Clinical Trials Involving Therapeutic Goods and the International Council for Harmonisation Good Clinical Practice guidelines [36, 68]. Adverse events will be collected by active capture (weekly during treatment [weeks 1 to 16] and during follow-up [week 26, week 52]), or by passive capture (participant report via telephone, email, or SMS). Data on adverse effects specific to memantine (those listed on the memantine product information), new medical conditions, or the worsening of existing medical conditions will be collected. Each adverse event reported will be assessed for:Seriousness: any medical occurrence that results in death; is life-threatening; requires inpatient hospitalisation or prolongation of an existing hospitalisation; results in persistent or significant disability/incapacity; is a congenital anomaly or birth defect; or is medically significant or important event or reactionCausality: whether the event has a reasonable causal relationship to the trial interventionExpectedness: whether the event is listed in the memantine product informationSeverity: mild/moderate/severe

The DSMB will periodically review overall safety data to determine trends of events or identify safety issues that would not be apparent on an individual case basis. A safety management plan will outline the flow and timelines for reporting all relevant safety information between the coordinating centre, the sponsor, the Human Research Ethics Committee, and the Australian Therapeutic Goods Administration.

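### The harm comparisons use no severity grade and leave the time window open, so an excess of graver adverse events, or one spread over several effects, could be missed

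*Protocol article*

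**What the plan says.** Under Secondary outcomes, the protocol article defines the harm outcome as "Adverse events, assessed as the number of participants with at least one adverse event, serious adverse event, or specific adverse event (yes/no"). On timing it says only: "Collected during treatment and during follow-up". The Main analysis section names the same three measures: "safety outcomes (the number of participants experiencing at least one adverse event, specific adverse events, serious adverse events) will be analysed in the same way". The scale is fixed too: "binary outcomes will be assessed as ratios of proportions", with 97.5% confidence intervals.

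The section on adverse event reporting and harms {22} shows how events reach these counts: "Adverse events will be collected by active capture (weekly during treatment [weeks 1 to 16] and during follow-up [week 26, week 52"]). Events that participants report unprompted, by phone, email or text message, are counted as well. Capture is broad, taking in effects listed for memantine, new conditions and worsening of existing ones. The same section has every event assessed for seriousness, causality, expectedness and severity (mild, moderate or severe).

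The severity grade appears in no harm outcome and no harm analysis. Discontinuations with reasons are to be shown for each comparison in the participant flow diagram (Descriptive analysis).

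**The concern.** Evaluating harms as well as benefits is the stated aim of the trial. The article also says that the memantine dose exceeds the one approved for Alzheimer's disease and is individualised to what each participant tolerates. How severe the events are therefore matters as much as whether any occurred.

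A yes/no count gives one mild event in one week the same weight as severe events in many weeks. Participants have at least moderate pain and disability, continue usual treatment and are asked about events every week, so many in both arms may record something minor. The any-event risk ratio then mostly reflects that shared background. The specific-event comparisons escape the dilution, but each covers one effect. An excess spread thinly over several effects leaves few events in each, and an excess in severity changes none of the yes/no answers.

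The open window adds to this. If treatment and follow-up are pooled, events from the 36 weeks after treatment (52 − 16) join the shared background and dilute an on-treatment excess.

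**Working it through.** **Inputs.** There are 204 participants allocated 1:1:1:1 (Trial design, Sample size), so 102 v 102 for each main comparison. The 97.5% intervals correspond to a two-sided level of 0.025, z = 2.241. The article gives no adverse-event rate and no power for harms, so it has no figure to reproduce. Every rate below is an assumption. Power is Φ[(difference − z·SE₀)/SE₁], with pooled SE₀ and unpooled SE₁.

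**Step 1: dilution by background.** Let B be a background risk common to both arms and d the risk of a drug-related event. With independence, the any-event risk is 1 − (1 − B)(1 − d). Take d = 10% v 25%:

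| B | Any event | Risk ratio | Power |
|---|---|---|---|
| 0 | 10% v 25% | 2.50 | 0.72 |
| 50% | 55% v 62.5% | 1.14 | 0.12 |
| 80% | 82% v 85% | 1.04 | 0.05 |
| 90% | 91% v 92.5% | 1.02 | 0.03 |

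The risk ratio also cannot exceed 1/(control risk): 1.25 at 80% and 1.11 at 90%.

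**Step 2: an excess in severity, spread over effects.** Assume moderate or severe events in 15% v 30%, a mild background of 80% in both arms, and an even spread over six independent effects.

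- Any event: 1 − 0.20 × 0.85 = 83% and 1 − 0.20 × 0.70 = 86%.
- One specific effect: 1 − 0.85^(1/6) = 2.67% and 1 − 0.70^(1/6) = 5.77%, about 2.7 v 5.9 participants.
- Moderate or severe: 15% v 30%.

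The plan is to read intervals rather than significance, so expected 97.5% limits are shown. They use SE(log RR) = √[(1 − p₁)/(102p₁) + (1 − p₂)/(102p₂)].

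| Comparison | Risk ratio | SE(log RR) | 97.5% limits | Power |
|---|---|---|---|---|
| Any event | 1.04 | 0.060 | 0.91 to 1.19 | 0.05 |
| One specific effect | 2.16 | 0.719 | 0.43 to 10.8 | 0.13 |
| Moderate or severe | 2.00 | 0.280 | 1.07 to 3.75 | 0.63 |

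With a lower mild background, the any-event comparison improves but stays weaker than the severity-based one. At 50% it is 57.5% v 65% (ratio 1.13, power 0.13). At 30% it is 40.5% v 51% (ratio 1.26, power 0.23).

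**Step 3: does weekly solicitation alone force a ceiling?** Suppose the drug doubles the weekly chance of any event. With independent weeks the 16-week risk is 1 − (1 − p)^16. The other rows let the weekly risk vary between people (beta distribution with parameters summing to 2 or 5).

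| Weekly risk | Clustering | 16-week risk | Risk ratio | Power |
|---|---|---|---|---|
| 10% v 20% | none | 81.5% v 97.2% | 1.19 | 0.93 |
| 10% v 20% | sum 5 | 54% v 80% | 1.48 | 0.96 |
| 10% v 20% | sum 2 | 39% v 64% | 1.63 | 0.91 |
| 15% v 30% | none | 92.6% v 99.7% | 1.08 | 0.65 |
| 15% v 30% | sum 5 | 70% v 92% | 1.32 | 0.97 |
| 15% v 30% | sum 2 | 53% v 80% | 1.49 | 0.96 |

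Five of the six cases keep power at 0.91 to 0.97, so an excess across all events would usually show. The weakness in Steps 1 and 2 arises when the excess lies in only part of what is counted.

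**Step 4: would a participant-week rate be better?** Not reliably. With a true weekly ratio of 1.5 and within-person correlation 0.3, its power against the yes/no measure is 0.34 v 0.42 at 10% weekly risk, and 0.94 v 0.59 at 30%.

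**The case against.** A reader might infer that 16 weekly solicitations must drive both arms to a ceiling and hide any real excess. The documents do not support that. They give no event rate, and Step 3 shows that allowing for clustering leaves the control arm at 39% to 70%. A 16-week risk ratio below the weekly ratio is also not a biased estimate: it is a different quantity, and the plan never claims to estimate the weekly one.

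A reader might also infer that extra clinician contact inflates passive reports in the graded motor imagery arm. Passive capture is defined as participant report by telephone, email or SMS. Nothing makes the telehealth sessions a reporting route, and active weekly capture applies to everyone. That bias is speculation.

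Three further points stand in part.

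- Specific and serious events are compared separately, and a concentrated excess would be seen: 10% v 30% in one effect gives a ratio of 3.0 and power 0.92. Six thin comparisons read together would flag at least one with chance 1 − 0.87⁶ = 0.57 if independent, but the false-alarm chance is then 1 − 0.975⁶ = 0.14 and each interval is very wide.
- Discontinuations with reasons will be reported for each comparison, so tolerability is not invisible. That is a flow count, however, and not an estimated harm effect with an interval.
- Severity tables and period splits may sit in supplementary tables that are not shown. But the article itself fixes the compared harm outcomes in two places, and neither uses severity or states the window.

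**Conclusion.** The concern holds in a limited form. The named harm comparisons (any, specific and serious events, yes/no) use no severity grade although every event is graded, and the window for the count is not fixed. If minor background events are common, an excess in severity or one spread over several effects could be missed by both the any-event and the single-effect comparisons. In the worked case, the any-event ratio is 1.04 with power 0.05, each specific effect has power of about 0.13, and a severity-based comparison has power 0.63.

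These figures rest on assumed rates: an 80% background of mild events, 15% v 30% moderate or severe events, and six independent effects of equal frequency. With rare background events the any-event loss is small. The primary outcomes are unaffected.

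**What to change.** Keep the planned outcomes and all reporting sources. Under Secondary outcomes and Main analysis, make these changes:

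- Add a comparison of participants with at least one moderate or severe adverse event, or an event leading to discontinuation of a trial intervention, during the 16-week treatment period.
- State the window for every yes/no harm count, with treatment-period events compared and follow-up events reported separately.
- Give risk differences beside risk ratios. This also helps where risks are near 1, since the log binary models planned for these outcomes can then fail to converge.
- Optionally, add a participant-week rate that allows for within-person clustering, labelled supplementary. Given Step 4, it should not be the main harm measure.

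The severity grades and discontinuation reasons are already collected, so no new data are needed. The cost is one or two more table rows and one more unadjusted harm comparison. Analysis is planned only after the last 52-week follow-up, anticipated in Q2 2027, so the change can be specified before true allocations are used.
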